#### Step V: Indwelling drainage

The pelvis is copiously irrigated with normal saline, the wound is checked again for no active bleeding, and a closed-suction drain is placed posterior to the anastomosis to be drawn out and fixed. The abdominal incisions are sutured layer by layer.

High-ligation group: IMV ligation at the pancreatic inferior border with root lymphadenectomy.

Following the steps described for the low-ligation group (including station 253 lymphadenectomy), the IMV is further mobilized cephalad to the inferior border of the pancreas and the root lymph nodes of the IMV are dissected (except above the left colonic artery, and the area along the distribution of the 253 lymph nodes is dissected). The main surgical steps are the same as those described above. The surgeon determines whether to perform radical rectal cancer resection and fistula surgery according to the intraoperative situation.

### Random and blinding

#### Randomization method

Randomization will be performed by using dynamic allocation with minimization. Age (<50, ≥50 years), sex (male, female), ASA score (I, II, III), tumor location (distance from the anal margin of the tumor; high: >10 cm, median: 5–10 cm, low: <5 cm), body mass index (<25.0, 25.0–29.9, ≥30.0 kg/m^2^), preoperative clinical stage (I, II, III), and neoadjuvant therapy (not performed, chemotherapy, radiotherapy, chemoradiotherapy) are assigned random numbers. Random number rule: 0001–1516.

#### Minimization of random formulas

Suppose a clinical trial has *N* treatment arms with *M* important prognostic factors, and the number of prognostic factor levels for each is *n*1, *n*2, … *n*r.

Assuming that a new patient is assigned to the *k*-th treatment group, the disequilibrium index of the whole system is *G_k_*, and the *G_k_* value is obtained by summing the *D_ik_* values of all intergroup imbalance indices at the patient level:

$$G_{k}=\sum_{i=1}^{M}W_{i}\times D_{ik}$$

Note: *i* is the *i*-th prognostic factor, *k* is the *k*-th treatment group, *M* is the total number of prognostic factors, and *W_i_* is the weight factor of prognostic factor *i*.

Let *D_ik_* be the amount of variation among the assignments of any given factor level:

$$D_{ik}=\frac{1}{N}\sum_{k=1}^{N}{\left(X_{ik}-\bar{X}\right)}^{2}$$

Note: *X_ik_* represents the number of subjects in the *k*-th treatment group and represents the mean number of subjects in each treatment group. The $\bar{X}$ group with the smallest *G_k_* value is taken as the target group. If the number of groups with the lowest *G_k_* value is greater than one, then one of the groups with the lowest *G_k_* value is selected as the target group with equal probabilities. To increase the uncertainty of the patient’s assignment to the target group, the probability of bias allocation is *P *= 0.8 to reduce selection bias.

If the result is calculated as *G_B_* > *G_A_*, then the probability that the patient will be assigned to Group A is 0.8 and the probability of being assigned to Group B is 0.2.

#### Blinding

Owing to the nature of surgical interventions, the surgeons and patients cannot be blindly assigned to the allocated ligation level. Outcome assessors (radiologists for imaging recurrence evaluation, pathologists for lymph node assessment) will not be informed of the treatment allocation and will complete evaluations by using standardized, de-identified imaging and pathological data only. Data analysts will be blinded to the treatment allocation.

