### Study endpoints

Main endpoint indicator: The 3-year DFS rate. Secondary endpoint measures include the following: lymph node yield; operative time; postoperative (30-day) morbidity (anastomotic leakage, incision site infection, postoperative abdominal hemorrhage, gastrointestinal bleeding, intra-abdominal infection, pulmonary infection, urinary system infection, chyle leakage, postoperative intestinal obstruction, cardiovascular event, cerebrovascular event, thrombotic disease, urination disorder, other) and mortality.

Adverse reaction indicators: The occurrence of postoperative complications and treatment measures will be recorded in detail. All adverse events will be recorded and those resulting in hospital admission, prolonged hospital stay, additional surgical or medical treatment, or death will be reported.

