#### Metric definitions

DFS: Defined as the time from surgery to tumor recurrence (local or distant) or death from any cause, whichever occurs first, and is assessed monthly.

Recurrence: Inclusive of local recurrence as a recurrence of a tumor in the pelvis or perineum and distant recurrence as a recurrence of a tumor other than in the pelvis.

Local recurrence of the tumor occurring in the surgical area, with or without an increase in tumor markers: a mass found at the anastomosis and identified by pathological biopsy. Distant recurrence of the tumor requires one of the following: signs of local tumor on colonoscopy or barium enema; imaging findings (ultrasound, chest X-ray, CT, MRI, bone scan, PET-CT, etc.) suggestive of recurrence; and the pathological results of needle biopsy at any site consistent with those of the primary tumor. If recurrence cannot be confirmed by imaging, it is considered confirmed by the expert review committee (the person in charge of the First Medical Center of the PLA General Hospital, the participating units including Peking Union Medical College Hospital and Peking University Cancer Hospital).

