#### Quality of surgery

Surgeons who participate in the study are required to follow the TME surgical principles (leave sharp scoring under direct vision in the presacral space; keep the pelvic visceral fascia intact; resect the whole mesorectum or make sure that the distal mesorectum of the tumor is not <5 cm and the extent of intestinal resection is ≥2 cm from the distal tumor) to complete radical rectal cancer resection. The following photos will be acquired during the operation to upload to the data system: IMV after free ligation (undissected IMV), after the third station lymphadenectomy, and *in vitro* specimen (including the intestinal tube and mesangium, with ruler or reference placed next to the specimen). In the HL group, 253 lymph nodes and IMV root lymph nodes will be dissected separately and sent for regular pathological examination, and, in the LL group, 253 lymph nodes will be dissected separately and sent for routine pathological examination. Surgeons need to evaluate the quality of the excised *in vitro* specimens. Referring to the concept of the quality grading of rectal cancer gross specimens proposed by Nagtegaal *et al.* [14], the criteria are as follows: (i) high-quality: mesorectal plane resection, intact mesorectum, no defect of >5 mm on the fascia surface of the pelvic visceral layer, no exposed muscularis of the intestinal wall, and a cylindrical appearance; (ii) moderate-quality: mesorectal internal plane resection, intact mesorectal, pelvic visceral fascia surface defect of >5 mm, no muscularis of the intestinal wall, sufficient mesorectal margins, and an approximately conical appearance; (iii) low-quality: myometrial propria plane resection, incomplete mesorectum, pelvic visceral fascia with a defect of >5 mm, and muscularis of the intestinal wall visible and conical in appearance.

The expert review committee (research initiator: the person in charge of the First Medical Center of the Chinese People’s Liberation Army General Hospital; participating members: the person in charge of Peking Union Medical College Hospital and the person in charge of Peking University Cancer Hospital) randomly select the research cases; after discussion, no fewer than two-thirds of the experts determine that the surgical quality meets the research requirements and the cases are qualified to be enrolled. If they do not meet the requirements of the enrolled surgical quality, they are excluded.

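### Pathologist blinding cannot hold for lymph node yield, because only the high-ligation arm sends a separate IMV-root specimen; blinding of the committee that settles uncertain recurrences is not stated

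*Protocol article*

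**What the plan says.** **Blinding.** The protocol article accepts that surgeons and patients cannot be blinded. It then names two groups of outcome assessors who are: radiologists evaluating recurrence on imaging, and "pathologists for lymph node assessment) will not be informed of the treatment allocation". The stated means is that they "will complete evaluations by using standardized, de-identified imaging and pathological data only".

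**Quality of surgery.** The nodal specimens differ by arm. "In the HL group, 253 lymph nodes and IMV root lymph nodes will be dissected separately and sent for regular pathological examination", whereas "in the LL group, 253 lymph nodes will be dissected separately and sent for routine pathological examination".

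**Study endpoints.** "Secondary endpoint measures include the following: lymph node yield" heads the list, so the pathologists' count is itself an endpoint.

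**Metric definitions.** Disease-free survival (DFS) counts recurrence or death. "If recurrence cannot be confirmed by imaging, it is considered confirmed by the expert review committee". Quality of surgery gives a committee of the same name, drawn from the same three institutions, a second task: it judges surgical quality in randomly selected cases and can have a case excluded.

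**The concern.** Blinding by de-identification works only if the material looks the same in both arms once the patient's identity is removed. Here one arm produces a container that the other never does, so a pathologist who is told nothing can still read the arm from the specimen list.

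This matters because node yield depends partly on how hard the pathologist searches. A reader who knows that a case had the more extensive dissection may search the mesorectum or station 253 more, or less, thoroughly. Yield also has consequences beyond its own comparison. The Adjuvant therapy section counts fewer than 12 nodes as a high-risk feature in stage II disease and treats stage III differently, so an arm-dependent search could reach treatment and, indirectly, DFS.

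The committee raises a separate and weaker question. The recurrences it confirms are primary-endpoint events, and the article does not say that it is kept unaware of the arm.

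**Working it through.** The plan gives no figure for this point, so there is nothing to reproduce and no formula applies. The check sets the sections side by side.

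**Pathologists**

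| Item | High ligation | Low ligation | Section |
|---|---|---|---|
| Station 253 nodes sent separately | yes | yes | Quality of surgery |
| IMV-root nodes sent separately | yes | no | Quality of surgery |
| Pathologist unaware of arm | claimed | claimed | Blinding |

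1. For any patient operated on and sampled as planned, a root container means high ligation and its absence means low ligation. The specimen set identifies the arm without any further clue.
2. The stated safeguard removes identity. It does not remove the container, and the article describes no relabelling, pooling or staged release.
3. Total yield is the sum of two parts: nodes from the field common to both arms (mesorectum plus station 253) and nodes from the IMV root. The between-arm difference in total yield is therefore (common field, high − common field, low) + (root, high). Only the bracketed term compares like with like and could be read blind. The last term exists in one arm by design.
4. The root term need not be small. The Discussion cites a prospective study in which 63 of 100 patients had nodes at the IMV root. A single total would mix a comparison that could be blinded with a quantity that cannot be.

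**Radiologists.** No section gives them arm-specific material. Their blinding stands as stated.

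**Committee**

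1. Blinding names radiologists and pathologists only. It makes no statement about the committee either way.
2. Metric definitions gives the committee the recurrences that imaging leaves unconfirmed.
3. Quality of surgery gives it the review of sampled cases, with exclusion as the possible outcome. Judging a ligation and dissection would probably show the arm, but the article does not say what material is reviewed.
4. The two roles meet only in a patient who is both sampled for quality review and later referred for uncertain recurrence. The article gives neither proportion, so no shift in the DFS effect can be calculated.

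**The case against.** **The asymmetry is the intervention.** Root dissection is what distinguishes the arms, so a root specimen in one arm only is unavoidable. This is right, and it is why blinding cannot be restored for the root nodes. It does not rescue the claim as written, which covers lymph node assessment without limit.

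**Pathologists are only said not to be informed.** Read literally, the promise can be kept while they work out the arm for themselves. But the purpose of the statement is assessment without knowledge of the arm, and that is not achieved.

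**A condensed article may omit specimen handling.** This is a fair defence on the committee: silence about how its packets are prepared contradicts nothing and may be answered in a fuller document. It is weaker on the pathologists, because the article states both the claim and the procedure that defeats it.

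**Stronger readings that a reader might infer.**
- That outcome-assessor blinding fails as a whole. The documents do not support this: nothing undermines the radiologists, who evaluate recurrence on imaging, and deaths need no such reading.
- That the committee judges cases on the ligation photographs. Operative photographs are uploaded to the data system and are required in the same section as the quality review, but the article never says that the committee uses them, and it reviews only sampled cases.
- That the committee's position biases the DFS hazard ratio by some stated amount. The share of events referred to it is not given, so any such figure would rest on invented inputs.

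**Conclusion.** The point holds for the pathologists. The Blinding and Quality of surgery sections conflict in effect, and lymph node yield is not protected by the blinding claimed for it. Unmasking is complete for every case sampled as planned. Its effect on node counts cannot be sized, because the documents give no expected yield and no measure of search effort. The proven reach is one secondary endpoint; any route to DFS through staging and adjuvant treatment is plausible but indirect.

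For the committee, the finding is a gap and not a broken statement. A body that decides some primary-endpoint events, and that also reviews surgical quality with power to exclude, has no stated blinding.

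The conclusion assumes that root nodes reach pathology as a recognisable separate specimen, as the article describes, and that no masking step exists which the article leaves out.

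**What to change.** **(a) Pathology.** In the Blinding section, limit the pathologist claim to the common field, mesorectum plus station 253. Send that material under a neutral code and have it read and recorded before the root container is released. Report lymph node yield in two parts: the common field as the blinded between-arm comparison, and the IMV root as an unblinded description in the high-ligation arm only. This works only if the main specimen does not itself show the ligation level, for example through the length of attached vein, so that should be checked when the coding is set up.

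**(b) Committee.** In Metric definitions, state that the committee judges recurrence from de-identified packets without the allocation, operative notes or operative photographs.

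**Cost.** Specimen coding at each centre, redaction of the packets, and a short delay in reading the root specimen. The packets change and the committee's membership does not, so no extra adjudicators are needed. Neither change affects surgery, treatment or sample size.

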#### Randomization

After the test is completed, the researcher logs in to the data access service (DAS) for the interactive web response system (IWRS) to apply for a random number and prints or downloads the randomization information of the DAS for the IWRS for storage. The stochastic flow chart is presented in Fig. 1.

**Figure 1 goag044-F1:**
[figure not shown]
Flowchart of the randomized allocation of study participants. This diagram illustrates the process of randomized participant allocation through an interactive web-based system, comprising two main stages: request and validation.

#### Randomly encoded files

Randomization form: At the end of randomization, the randomization form is exported from the IWRS, submitted to the sponsor, and sealed. Upon study database lock and sponsor approval, a randomization list is generated and provided to the project statistician.

#### Enrollment

In this study, a competitive enrollment method has been adopted and the dynamic minimization method will be used to control the bias of the randomized patients, such as age, sex, ASA, tumor location, body mass index, preoperative clinical stage, and neoadjuvant therapy (the weights of the seven factors are the same; the optimal allocation probability is *P *= 0.8 and the variance will be used to measure the size of the imbalance between the groups), and dynamic minimization enrollment will be achieved via an interactive network response system.

### Study endpoints

Main endpoint indicator: The 3-year DFS rate. Secondary endpoint measures include the following: lymph node yield; operative time; postoperative (30-day) morbidity (anastomotic leakage, incision site infection, postoperative abdominal hemorrhage, gastrointestinal bleeding, intra-abdominal infection, pulmonary infection, urinary system infection, chyle leakage, postoperative intestinal obstruction, cardiovascular event, cerebrovascular event, thrombotic disease, urination disorder, other) and mortality.

Adverse reaction indicators: The occurrence of postoperative complications and treatment measures will be recorded in detail. All adverse events will be recorded and those resulting in hospital admission, prolonged hospital stay, additional surgical or medical treatment, or death will be reported.

#### Metric definitions

DFS: Defined as the time from surgery to tumor recurrence (local or distant) or death from any cause, whichever occurs first, and is assessed monthly.

Recurrence: Inclusive of local recurrence as a recurrence of a tumor in the pelvis or perineum and distant recurrence as a recurrence of a tumor other than in the pelvis.

Local recurrence of the tumor occurring in the surgical area, with or without an increase in tumor markers: a mass found at the anastomosis and identified by pathological biopsy. Distant recurrence of the tumor requires one of the following: signs of local tumor on colonoscopy or barium enema; imaging findings (ultrasound, chest X-ray, CT, MRI, bone scan, PET-CT, etc.) suggestive of recurrence; and the pathological results of needle biopsy at any site consistent with those of the primary tumor. If recurrence cannot be confirmed by imaging, it is considered confirmed by the expert review committee (the person in charge of the First Medical Center of the PLA General Hospital, the participating units including Peking Union Medical College Hospital and Peking University Cancer Hospital).

### Postoperative follow-up

Follow-up will be conducted in accordance with the Chinese Guidelines for the Diagnosis and Treatment of Colorectal Cancer (2020) [8] and will be tailored to patient compliance. The follow-up plan of this study is as follows: (i) History and physical examination and monitoring of carcinoma embryonic antigen and carbohydrate antigen 19-9 every 6 months for 3 years and then annually for a total of 5 years, followed by annually after 5 years. (ii) CT or MRI of the chest/abdomen/pelvis every 6 months for 3 years and then annually for 5 years. (iii) Colonoscopy should be performed within 1 year after surgery. If there is any abnormality, colonoscopy will be reperformed within 1 year; if no polyps are found, reexamination will be performed within 3 years and then once every 5 years. Resection of colorectal adenomas that appear on follow-up examination is recommended. If the colonoscopy does not complete the full-colon examination before surgery, then colonoscopy is recommended to be performed 3–6 months after surgery. (iv) PET-CT is not routinely recommended but may be considered in patients with preexisting or suspected recurrence and distant metastases to further confirm recurrence and metastasis.

More frequent follow-up visits can be performed on the basis of patient compliance; other examinations, such as bone scans and liver MRI, can be improved according to the actual situation of the patient; if it is difficult to complete thoracic/abdominal CT, then chest X-ray and abdominal ultrasound must be completed to confirm the recurrence and metastasis of the liver and lungs.

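### An unconfirmed chest X-ray or ultrasound finding can count as a distant DFS event on the same footing as CT or MRI, and the trigger for using those tests is undefined

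*Protocol article*

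**What the plan says.** Under Study endpoints the primary endpoint is fixed: "Main endpoint indicator: The 3-year DFS rate". Under Metric definitions, DFS runs from surgery to local or distant recurrence or death from any cause.

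The Postoperative follow-up section schedules "CT or MRI of the chest/abdomen/pelvis every 6 months for 3 years". Its closing paragraph adds the fallback: "if it is difficult to complete thoracic/abdominal CT, then chest X-ray and abdominal ultrasound must be completed to confirm the recurrence and metastasis". The stated targets of the fallback are the liver and the lungs. The section does not say what makes CT difficult. It also says that follow-up is adapted to patient compliance.

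Metric definitions introduces the criteria for distant recurrence as a list of which one is required. One entry is "imaging findings (ultrasound, chest X-ray, CT, MRI, bone scan, PET-CT, etc.) suggestive of recurrence". No modality ranks above another. Recurrence that imaging cannot confirm goes to the expert review committee.

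The Blinding section says that surgeons and patients cannot be blinded. Outcome assessors, including the radiologists who judge recurrence, are not told the allocation and "will complete evaluations by using standardized, de-identified imaging and pathological data only".

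**The concern.** Three provisions meet at the primary endpoint and do not fit together well. The follow-up section allows weaker tests in place of thoracic or abdominal CT under a trigger that is not defined. The endpoint definition lets a merely suggestive finding on those tests count as a distant event. The blinding section promises standardized imaging, yet the mix of modalities can vary between patients with compliance and with what is judged difficult.

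Two consequences follow for DFS:

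- **Dilution.** If the fallback is used equally in both arms, false-positive liver or lung findings add events unrelated to ligation level and pull the hazard ratio towards 1.
- **Bias.** If it is used unequally, the arm with more X-ray and ultrasound visits collects more false events. With surgeons and patients unblinded, equal use cannot be taken for granted.

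This is a stated event rule, so it is not a detail that the protocol leaves to an analysis plan.

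**Working it through.** **1. Does a suggestive X-ray or ultrasound finding suffice?** The distant-recurrence list ends with *and* before its pathology entry, but it is introduced as requiring one of its entries. On that wording the imaging entry is enough without pathology. Committee review is reserved for recurrence that imaging cannot confirm. A suggestive ultrasound already meets the imaging entry, so the text does not clearly send it to the committee.

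**2. Reproducing the planned sample size.** Inputs from Number of research cases: 3-year DFS 85% and 78%, margin 0.90, two-sided α 0.05, 2-year enrolment, 3-year follow-up, 20% loss. I take power as 80%, survival and loss as exponential, and the 20% loss as accruing over 3 years (assumptions).

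- Hazards per year: −ln(0.85)/3 = 0.0542 and −ln(0.78)/3 = 0.0828, so HR = 0.654. Loss: δ = −ln(0.80)/3 = 0.0744.
- Event probability: P = λ/(λ+δ) × [1 − (e^(−3(λ+δ)) − e^(−5(λ+δ)))/(2(λ+δ))] = 0.1687 and 0.2448, mean 0.2067.
- Freedman: θ = 0.654/0.90 = 0.7268. Events = (1.960 + 0.842)² × [(1+θ)/(1−θ)]² ≈ 313.5. N = 313.5/0.2067 ≈ 1,516, the planned total.
- Power with d = 313 events: Φ[(ln 0.90 − ln 0.654) × √d/2 − 1.96] = 81%.

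**3. Adding false-positive events equally in both arms.** The protocol gives no fallback share and no error rate. I assume that a share s of patients use the fallback at all six visits to month 36, with false-positive rate f per visit over and above CT or MRI.

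- Disease-free patients given a false event by month 36: q = s × [1 − (1−f)⁶]. The bracket is 0.0585 at f = 1% and 0.1142 at f = 2%.
- Observed DFS: 0.85(1−q) and 0.78(1−q). HR is the ratio of their logarithms. Events and power are recomputed as in step 2.

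| s | f | q | HR | Events | Power |
|---|---|---|---|---|---|
| 0 | – | 0 | 0.654 | 313 | 81% |
| 10% | 1% | 0.6% | 0.662 | 321 | 79% |
| 10% | 2% | 1.1% | 0.669 | 329 | 77% |
| 20% | 1% | 1.2% | 0.670 | 329 | 76% |
| 20% | 2% | 2.3% | 0.684 | 344 | 72% |
| 30% | 1% | 1.8% | 0.677 | 337 | 74% |
| 30% | 2% | 3.4% | 0.697 | 359 | 68% |

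**4. Unequal use with no true effect.** Take 78% DFS in both arms and f = 2%, with 10% use in the high-ligation arm and 30% in the low-ligation arm. Observed DFS is 0.78 × (1 − 0.0114) = 0.771 against 0.78 × (1 − 0.0342) = 0.753. The apparent HR is ln(0.771)/ln(0.753) ≈ 0.92. With the shares exchanged it is 1/0.92 ≈ 1.09.

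**The case against.** The strongest reply is that the effect cannot be sized from the documents. Every input in steps 3 and 4 of the check is assumed. The model puts the same patients on the fallback at every visit, never reverses a false positive, and carries the same hazard past month 36, when imaging becomes annual. The fall to 68% needs the most extreme corner; the mildest gives 79%. Nothing in the protocol suggests that use will differ by arm. PET-CT may be considered for suspected recurrence, and the committee exists. All of this stands as a limit on size. It does not remove the rule: PET-CT is optional, and committee review is tied to imaging that fails to confirm.

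A second fair objection is that demanding confirmation by CT, MRI or biopsy, in the very patients for whom CT was difficult, could lose or delay true recurrences. The fix must allow for that.

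A reader might infer more than the text supports:

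- **That the fallback leaves the pelvis unexamined.** It is triggered by difficulty with thoracic or abdominal CT and is aimed at liver and lungs. Nothing waives the scheduled pelvic CT or MRI, and local recurrence is defined separately, through an anastomotic mass proven by biopsy.
- **That these tests are read at the site, or that unblinded people choose them.** The protocol says neither. It provides for radiologists unaware of allocation and makes no exception for ultrasound or X-ray.
- **That an ultrasound cannot be re-read blind.** No section says so. The protocol is only silent on how ultrasound meets its standardized-imaging requirement.
- **That a negative fallback visit is coded disease-free, so that DFS is overstated.** No coding or censoring rule for such visits is given, and that is commonly left to the analysis plan.

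**Conclusion.** The point holds in a limited form. An undefined trigger admits chest X-ray and ultrasound for liver and lung surveillance, and the endpoint definition counts a suggestive finding on them as a distant DFS event, level with CT or MRI and without confirmation. That sits poorly with the standardized evaluation promised under Blinding.

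The size is unknown. Under the assumed 10–30% substitution and 1–2% excess false positives per visit, the hazard ratio moves from 0.654 to 0.66–0.70 and power from 81% to 79–68%. Equal use dilutes the effect. Unequal use could produce an apparent difference where none exists, about 0.92 in the example, but the documents give no evidence that use would be unequal.

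The reading that DFS as a whole rests on weak evidence is not supported. The issue is confined to liver and lung findings at visits where the fallback is used, and deaths are unaffected. The change is worth making because the rule is explicit and cheap to tighten. Confidence is medium.

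**What to change.** Leave the clinical fallback as it is, and reconcile Blinding, Metric definitions and Postoperative follow-up for the endpoint only.

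1. In Metric definitions, state that a finding seen only on chest X-ray or ultrasound counts as a DFS event when it is confirmed by CT, MRI or biopsy done in routine work-up. Where none of these is available, the existing expert review committee decides without knowledge of allocation. Date the event at the first suspicious finding. The committee route keeps true recurrences in patients for whom CT is difficult, and no procedure is added.
2. Record the imaging modality at each visit and report fallback use by arm. Add a sensitivity analysis of DFS that censors patients without an event at their last CT or MRI.

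The cost is revised endpoint wording, one case report form field, some committee time and one extra analysis. A few events will wait for confirmation or review, and the sensitivity analysis gives up some follow-up time.
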